### **Blood sample on V1**

The blood sample will be used to measure the various biological parameters detailed in section 7.3, and in particular the parameters concerning the hepatic and renal functions of the participant.

Blood sampling for liver, kidney function and blood sugar must be done after the consent is signed and before the first PET scan is performed. The results must be known to the investigating physician before these examinations are performed. The interpretation of the results (in particular via the calculation of the glomerular filtration rate) concerning liver, kidney function and blood sugar will be the responsibility of the investigating physician and will condition the performance of the PET imaging examinations during the V1 visit. A biological abnormality of grade 3 or higher constitutes a criterion of ineligibility for the trial.

At this time, the sample required for GWAS and APOE genotyping will also be collected, which will be specified in the consent.

The sample will be taken in the morning at the CRC of the University Hospital of Caen. Due to the constraints related to the determination of some of the blood biomarkers, it will be necessary that the sample is collected in the morning between 8 and 10 am, on an empty stomach, and after one day of diet excluding foods rich in serotonin (tomatoes, citrus fruits, dried fruits, avocados, pineapples, plums, chocolate and bananas). The participant will be reminded of the instructions concerning the diet prior to this sampling.

On the day of the sampling, each participant will join their referent at the CRC of the CHU of Caen. Once the sample has been taken, the participant will be invited to have a snack if they need to continue with another examination.

All the tubes collected (maximum total volume of 68 mL) will then be transmitted directly by the CRC of the University Hospital of Caen to the various laboratories responsible for the analyses (see section 7.3).

### **Brain imaging examinations in MRI**

Two MRI sessions will be offered to all participants (meditating experts and non-expert seniors). A third session will be offered only to the group of meditating experts. All MRI sessions will take place at the Cyceron center in Caen and the three sessions will always be conducted successively, as indicated below (MRI session 1 will always precede MRI session 2, which will precede MRI session 3). Prior to each MRI session, the participant will be reminded (by phone and/or during the previous visit)

that they must limit their consumption of coffee before the examination, present themselves without make-up, hair spray or gel, and that all jewelry or metallic objects must be removed before entering the MRI.

### ***MRI1 session***

The MRI1 session will always be performed at the beginning of the protocol, after the consent signature (performed at the beginning of the inclusion visit) and before any other examination at the inclusion visit. The sequence of this MRI session is shown in Figure 7. Upon arrival at the Cyceron center, the participant will be greeted by their referent, who will remind them of the upcoming examination. The participant will then be asked to complete a self-assessment questionnaire (STAI-A, Spielberger et al., 1983). This questionnaire makes it possible to evaluate "state anxiety", i.e. at the very moment when the participant fills it out. As the anxiety-state may change from one appointment to another, it will be proposed several times. The participant will then be asked to put on pyjamas, leave clothing and any jewelry, glasses or dental/auditory appliances in a secure changing room, thus ensuring that no metallic material is present at the MRI. Blood pressure, weight, height, abdominal circumference and hip circumference will be measured during this step (measurements used as indices in the measurement of cardiovascular risk). Before entering the MRI, the participant will be provided with disposable earplugs to reduce noise from the machine. The participant will then be placed in the MRI by the radiology manipulators.

The rest-SoVT task (proposed in fMRI at the end of this first MRI session) will then be explained to the participant. The instructions will be given to the participant, who will then be invited to perform a short training session on the computer, in order to make sure that the instructions are well understood. In total, this training will take about 10 minutes.

The details of the MRI sequences for the first session are shown in Figure 7 below. After a baseline scan, the first part of the examination will be devoted to anatomical acquisitions, for a duration of approximately 35 minutes. These anatomical acquisitions will include a T1-weighted sequence, a T2-weighted hippocampal targeted sequence (T2 HCP), a T2-weighted sequence and a FLAIR sequence.

A 10-minute resting fMRI sequence will be proposed. During the fMRI examination, brain function will be assessed at rest (as opposed to during an activation task). No task is proposed and the participant will be asked to "keep eyes closed, don't sleep and let thoughts flow freely". However, the instruction given to the meditating experts will invite them to perform this sequence in a meditative state. For half of the experts, the sequence will be performed in a state of mindfulness meditation, for the other half it will be performed in a state of compassionate meditation. The experts who performed the sequence in a state of mindfulness meditation during this session will perform it in a state of compassionate meditation during the MRI3 session (see below), and vice versa for the other half of the experts. This functional sequence will be preceded by a T2\*-weighted sequence, necessary for the pre-processing of the fMRI data.

The MRI examination will be followed by an activation fMRI acquisition during which the rest-SoVT task will be proposed. During the rest-SoVT task, participants will be asked to watch short videos (less than 20 seconds), either neutral or emotional (people expressing a suffering emotion). A total of

24 videos, divided into 8 series, will be presented. For each series of videos, a period of exposure, corresponding to the successive presentation of 3 videos expressing the same emotion, will be followed by a 90-second rest period (fixation cross). The participant will be instructed to press a button before each series of three videos and then to watch the videos that follow (see Figure 6). For expert meditators, this rest-SoVT session will be performed in a neutral state (compared to the same task performed in different meditative states, as proposed in Session MRI3, see below). The series of neutral and emotional videos will be presented alternately and the order of presentation will be randomized across participants. In total, the test will last 17 minutes.

The total duration of the examination (anatomical acquisitions + fMRI) will be approximately 60 minutes.

At the end of the acquisition, the participant will be asked to leave the MRI and take back their personal belongings. Finally, each participant will have to watch again, this time outside the MRI, the 24 videos presented during the rest-SoVT task and judge for each of them how much empathy, positive emotions and negative emotions they felt.

[figure not shown]

Figure 6: Representation of the different conditions of the rest-SoVT task

[figure not shown]

Figure 8: MRI 1 examination procedure (the time spent in the MRI is shown in orange with a total duration at the Cyceron center  $\approx 120$  min)

## MRI2 session

The procedure for the second MRI session is shown in Figure 9. Upon arrival at the Cyceron center, the participant will be greeted by their referent, who will remind them of the upcoming examination. As with MRI1, the participant will be asked to complete a self-anxiety questionnaire (STAI-A) and a blood pressure measurement will be performed. Participants will then be familiarized with the AX-CPT task, proposed in fMRI during this second MRI session. A short training session on the computer will be proposed to ensure that the instructions are well understood. Then, the participant will be invited to put on pyjamas (leaving clothes and possible jewels, glasses or dental/auditory devices in a secured locker room) and to put earplugs (to attenuate the noise generated by the MRI) before being installed in the MRI by the radiology manipulators.

The details of the MRI sequences are shown in Figure 10 below. The session will start, after a baseline scan and a T2\*-weighted sequence (necessary for fMRI preprocessing), with a functional acquisition with the AX-CPT task. During this attentional test, letters written in black or grey scroll on the screen. The participant is instructed to press a particular key when a black "X" (target) appears after a black "A" (cue). For all other letter combinations, he must press another key. Two conditions will be proposed: an easy condition and a difficult condition. In the easy condition, the attentional load is said to be low because no distraction appears between the target and the clue. In the difficult condition, the attentional resources are strongly engaged by the addition of distracting letters, written in grey, between the cue and the target. In 25% of the cases, the trials will be valid (letter "X" preceded by an "A" - "AX"), reflecting phasic alertness abilities. The remaining 75% of trials will be invalid. In 1/3 of the cases, these will be control trials where the letter "Y" has been preceded by a letter "B" ("BY" = invalid index and target), 1/3 will evaluate the inhibition abilities of the item where the letter "X" is preceded by a "B" ("BX" = invalid cue but valid target) and the last third of the trials will evaluate the inhibition abilities of the context where a "Y" will appear after a letter "A" ("AY" = valid cue but invalid target) A total of 200 trials will be offered (100 in the easy condition and 100 in the difficult condition), and for each condition the different types of trials will be presented randomly. Overall, the AX-CPT task will last approximately 23 minutes.

The session will continue with an anatomical acquisition of approximately 21 minutes including a diffusion sequence (DKI for Diffusion Kurtosis Imaging), a magnetic susceptibility sequence (QSM for Quantitative Suceptibility Mapping) and a perfusion sequence (ASL for Arterial Spin Labeling).

In total, the acquisition time of the MRI2 session should be about 60 minutes.

At the end of the acquisition, the participant will be invited to leave the MRI, to collect his personal belongings. They will then be able to leave.

[figure not shown]

Figure 9: Representation of the different conditions of the AX-CPT task

[figure not shown]

Figure 10: MRI2 examination procedure (time spent in the MRI is shown in orange with a total duration at the Cyceron center  $\approx$  120 min)

### MRI3 session (Experts only)

This 3rd MRI session is only offered to meditative experts. Upon arrival at the Cyceron center, the participant will be greeted by their referent, who will remind them of the upcoming examination. As in other sessions, the participant will be asked to fill out a self-anxiety questionnaire (STAI-A) and a blood pressure measurement will be taken. During this MRI session, the participant will be familiarized with the rest-SoVT task, and will then be asked to put on pajamas (leaving clothing and any jewelry, glasses or dental/auditory appliances in a secure locker room) and put in earplugs (to attenuate the noise generated by the MRI) before being installed in the MRI by the radiology manipulators.

The details of the MRI sequences are shown in figure 11 below. During this session, fMRI sequences will be acquired. The session will start with a first fMRI sequence at rest, for which no specific instructions will be given. A second fMRI sequence at rest will then be proposed and the participant will be asked to perform it in a state of mindfulness meditation if the same sequence was performed in a state of compassionate meditation during the MRI2, and vice versa for the second half of the participants. Subsequently, the participants will be asked to perform the rest-SoVT task again, (see MRI1 session) twice, in a different meditation state. Half of the participants will first perform the task in a mindfulness meditation state and then in a compassionate meditation state. The other half of the participants will perform these tasks in the other order (compassionate meditation then mindfulness). Each resting fMRI sequence will last 10 minutes and each activation fMRI sequence (rest-SoVT) 17 minutes.

Overall, the acquisition time for this last session will be approximately 60 minutes.

At the end of the acquisition, the participant will be invited to leave the MRI and take back his personal belongings. Finally, as for the MRI1 session, each participant will have to watch again, this time outside the MRI, the 48 videos presented during the two rest-SoVT tasks and judge for each of them how much they experienced empathy, positive emotions and negative emotions.

[figure not shown]

Figure 11: MRI3 examination procedure (time spent in the MRI is shown in yellow with a total duration at the Cyceron center ≈ 130 min)

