### 5.2. Secondary evaluation criteria

- Behavioural measurements (OBJECTIVES 2, 4, 6, 7, 9) :

a composite score per function assessed by the neuropsychological tests and questionnaires (listed in Tables 5 and 6 below, see section 6.7). The composite scores will be an average of z-scores calculated from all scores collected for the corresponding function that have a normal distribution and do not show a floor/ceiling effect. (In addition, exploratory analyses will be conducted on all individual behavioural measurements collected).
- Imaging measurements (OBJECTIVES 2, 4, 6, 7, 8, 9):
  - Volume of gray matter in each brain voxel;
  - Volume of the hippocampus and hippocampal subfields;
  - Brain perfusion measure in each brain voxel;
  - Fractional anisotropy and mean diffusivity in each brain voxel;
  - Number, size and location of white matter lesions;
  - Magnetic susceptibility measured in each brain voxel;
  - Functional brain connectivity in a non-meditative state;
  - Beta-amyloid load (from the radiopharmaceutical Amyvid® ) measured in each brain voxel and global average in the gray matter;
  - Cerebral glucose consumption at rest (relative to the average consumption measured in the cerebellum)
  - Brain activity measured in fMRI specifically associated with emotional processing (comparing emotional and neutral items) from the Rest-SoVT task.
  - Brain activity associated with attentional processus of alertness, inhibition and sustained attention measured in fMRI during the AX-CPT task.
  - Spontaneous oscillatory activity (EEG) in a resting state.
  - EEG brain activity specifically associated with the processing of auditory stimuli (MMN protocol).
- Sleep measurements (OBJECTIVES 2, 4, 6, 7, 9):
  - Subjective sleep measurements collected by sleep questionnaires (Tables 6 and 7 below)
  - Actimetry parameters (average sleep duration, fragmentation index of activity and rest periods, regularity of activity/rest cycle).
  - Data collected through polysomnographic recordings
  - Data collected with the Somno-Art device.
- Biological measurements (OBJECTIVES 2, 4, 6, 7, 9):
  - Blood measurements as listed in Table 8 below, see section 7.3. 4 (such as total cholesterol, BNP, bioavailable testosterone, serotonin, estradiol, SHBG, SDHEA, cytokines, cortisol,

- telomere length, telomerase activity, A $\beta$  1-42, Tau/phosphoTau proteins, tPA and BDNF, fibrinogen and GFAP)

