#### **Functional MRI (resting and activation):**

Dynamic functional acquisitions will be acquired both during activation fMRI sessions (AX-CPT and rest-SoVT) and during resting fMRI sessions. For each participant, as many functional acquisitions as there are fMRI sequences will be collected in electronic format, namely:

- *For non-expert seniors:* a functional acquisition of activation during the rest-SoVT task, a functional acquisition of activation during the AX-CPT task and a functional acquisition at rest.
- *For the expert meditators:* three functional acquisitions of activation during the rest-SoVT task (one for each meditation condition), one functional acquisition of activation during the AX-CPT task and three functional acquisitions at rest SoVT (one for each meditation condition).

These acquisitions will allow the study of brain function during the different tasks (attention and emotions) as well as functional connectivity. A brain volume of each participant will be acquired approximately every 2 seconds during all the fMRI sessions, thus allowing to measure the evolution of the cerebral neuronal activity in the same voxel over time. Indeed, the measurement of cerebral neuronal activity in fMRI is done through the BOLD signal which corresponds to an increase in the local blood concentration of deoxyhemoglobin (Logothetis et al., 2004). These concentration changes locally perturb the magnetic field and these perturbations are collected through the T2\* weighted Echo Planar Imaging sequence every 2 seconds or so.

These functional acquisitions will be accompanied by a T2\* acquisition (one for each different MRI session). This acquisition is necessary for the preprocessing (registration) of the functional imaging data and will also be collected in electronic format. Consequently, the following data will be collected:

- *For non-expert seniors*: two acquisitions in T2\*.
- *For the experts*: three acquisitions in T2\*.

In addition, the following will be collected during activation fMRI examinations:

- Behavioural performance on the AX-CPT task (accuracy measure and reaction time)
- The results of the post-scan debriefings of the rest-SoVT task (video judgment scores)

All these acquisitions will be collected on the MRI of the Cyceron Center.

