### **Objective 4 (WP 1 to 6)**

All cognitive measures, psychoaffective measures, life factors, blood, sleep and imaging measures at inclusion will be compared between the group of expert in meditation and the non-expert seniors. (see Section “*Descriptive analysis*” above for comparative methods)

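### The non-meditative resting connectivity compared between experts and seniors comes from differently described scans in different sessions, so group is fully aligned with session, position and, read literally, instruction

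*Combined protocol and SAP*

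**What the plan says.** Protocol Section 5.2 lists "Functional brain connectivity in a non-meditative state" among the imaging criteria that serve Objective 4 (among others). The secondary-objectives SAP lists the equivalent voxel-wise outcome under its radiological outcomes. For Objective 4 that SAP states: "All cognitive measures, psychoaffective measures, life factors, blood, sleep and imaging measures at inclusion will be compared" between experts and non-expert seniors.

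The resting scans are described in protocol Section 6.6:

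- **MRI1 session, all participants.** A 10-minute resting run in which the participant is asked to "keep eyes closed, don't sleep and let thoughts flow freely". It is described after the anatomical block: "the first part of the examination will be devoted to anatomical acquisitions, for a duration of approximately 35 minutes".
- **MRI1 session, experts.** "However, the instruction given to the meditating experts will invite them to perform this sequence in a meditative state". Half practise mindfulness and half compassion.
- **MRI2 session.** No resting run is described.
- **MRI3 session, experts only.** "The session will start with a first fMRI sequence at rest, for which no specific instructions will be given". A second resting run follows, in whichever meditative state the expert has not yet performed. The text ties that choice to whether the expert was in the other state: "if the same sequence was performed in a state of compassionate meditation during the MRI2".

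Protocol Section 10.1.2, on functional MRI data, lists for experts "three functional acquisitions at rest SoVT (one for each meditation condition"). The wording is muddled, but rest-SoVT acquisitions are counted separately in the same sentence, so this reads as three resting runs, one per condition.

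**The concern.** The two groups share an outcome name but not a described procedure. Seniors have a scripted run. The experts' corresponding run, read literally, has no script, and it falls in a different session at a different point. By eligibility, experts meditate at least 6 days a week for at least 45 minutes a day on average. Nothing in the MRI3 text tells them what to do with their eyes or attention in the run that has to represent their non-meditative state.

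A connectivity difference produced by session, position or instruction would be read as an association with expertise. The risk of misreading is greater because protocol Section 1.2.4 already cites altered resting connectivity in expert meditators, so an artefact could look like confirmation.

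**Working it through.** **Which expert run can serve the comparison.** Experts have three resting runs, one per condition. The MRI1 run is meditative, and so is the second MRI3 run. Only the first MRI3 run remains.

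**The two runs side by side, from Section 6.6.**

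| Feature | Seniors | Experts |
|---|---|---|
| Session | MRI1 | MRI3, which always follows MRI1 and MRI2 |
| Position | Described after about 35 minutes of anatomical imaging | First run of the session |
| Earlier resting run in the study | None | One, meditative, in MRI1 |
| Instruction as written | Eyes closed, awake, free thought | Nothing specific |

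Each row takes one value for all seniors and another for all experts. Procedure and group are therefore the same variable in this contrast. Adding age, sex, education or MMSE to the model does not separate them.

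**The plan's own power for this comparison (protocol Section 11.2).** Inputs: 30 experts, 126 seniors, alpha 5% two-sided. The noncentrality is d × √(30 × 126 / 156) = d × 4.92, and power is approximately Φ(d × 4.92 − 1.96).

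- d = 0.74: 95.4% (noncentral t 95.2%); stated 95%.
- d = 0.67: 91.0% (t 90.6%); stated 90%.
- d = 0.58: 81.5% (t 81.0%); stated 80%.

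The stated figures reproduce and are not in dispute.

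**Illustration of what a procedural shift would do.** The documents give no size for such an effect, so the shift is an assumption. With no true expertise effect, the same noncentral t calculation (30 versus 126) gives these rejection rates at a nominal 5%:

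| Assumed shift (SD) | Rejection rate |
|---|---|
| 0 | 5.0% |
| 0.1 | 7.8% |
| 0.2 | 16.5% |
| 0.3 | 31.2% |
| 0.5 | 68.7% |

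With 150 seniors instead of 126, shifts of 0.2 and 0.3 SD give 16.9% and 32.0%. These rates hold for one t test on one scalar measure. The secondary SAP plans seed-based and independent component analyses, so they show direction and sensitivity and do not estimate this trial's error rate.

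**The counterbalancing sentence.** The MRI3 text places the experts' earlier meditative resting run in MRI2. The MRI2 description contains the AX-CPT task plus diffusion, susceptibility and perfusion sequences, and no resting run. The MRI1 text places that run in MRI1. The two passages contradict each other, and the MRI1 account is the one that fits the listed sequences. This concerns the meditative runs and is a separate, clerical matter.

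**The case against.** The strongest reply is that the MRI3 phrase may mean only that no meditation instruction is given. It stands immediately before a run performed in an instructed meditative state, so that is its natural contrast. The same section says that instructions for the tests proposed in functional MRI are standardized. The MRI1 script can be read as describing the resting sequence in general, with the experts' meditation invitation as an addition. The MRI3 figure is also missing from the copy available, and it may hold more detail. A reader might infer that experts were scanned with eyes open, or were meditating, and that the comparison is shown to be confounded by instruction. No text says so, and that reading is not supported.

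This reply does not close the point. The standardization statement refers to tests, while the MRI1 text says that no task is proposed at rest, and it does not say that the MRI1 and MRI3 resting instructions match. For the rest-SoVT task in MRI1 the protocol does specify a neutral state for experts; for this run it specifies nothing. The session and position differences remain however the phrase is read.

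It is also fair that Objective 4 sits among the more exploratory objectives, in a non-randomized cross-sectional comparison, and that this is one imaging outcome among many. That limits the consequence and does not remove it.

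**Conclusion.** As written, the Objective 4 comparison of non-meditative resting connectivity sets a scripted first-session run against a third-session opening run described without specific instructions. Group is fully aligned with session and position. On the literal text it is also aligned with instruction. The first part is established; the second depends on what experts were actually told, which the documents do not settle.

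The size of any bias is unknown. The rejection rates above rest on assumed shifts in a single t test. A reader might take them as this comparison's false-positive rate, but the documents give no basis for that.

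Nothing here reaches the primary endpoints, which are volume and perfusion, or the randomized comparisons. All three randomized arms follow the same MRI1 procedure at inclusion, and the 18-month visit repeats the MRI sessions in every arm.

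**What to change.** 1. **Protocol Section 6.6, MRI3 session.** Replace the statement about instructions for the first resting run with the same script as in MRI1. Add no wording for experts only: telling experts not to meditate, when seniors are not told so, would create a new instruction difference aligned with group.
2. **Same paragraph.** Correct MRI2 to MRI1 in the counterbalancing sentence.
3. **Secondary SAP, Objective 4.** Name the first MRI3 resting run as the experts' run for non-meditative connectivity.
4. **Experts already scanned.** Establish from the scan procedure and site records what they were told, and document it.
5. **Reporting.** Present the contrast as potentially confounded by session and position, and by instruction where the script was not given, and not as an effect of expertise alone.

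The cost is a few sentences, a check of records and no extra scan. The limit is timing. The Lockdown annex counts 25 experts included on 8 April 2020 out of a planned 30. Protocol V12.0 is dated 07/01/2022, and Section 3.3 ends expert recruitment in February 2022. A new script could reach about 30 − 25 = 5 experts at most, too few for a useful subgroup. For the others the remedy is labelling and a weaker conclusion. The session and position differences cannot be removed for anyone under the present design.
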